## Abstract

We will study the influence of low intensity and frequency surface peripheral electrical stimulation (PES) on nerve regeneration of digital nerve injuries of the hand after its surgical repair in humans. Participants will be patients with acute traumatic peripheral nerve injury referred to the Hand Surgery Service of the General Hospital of the State of Bahia, a reference service in the state. These patients will undergo surgery followed by PES in the immediate postoperative period. After hospital discharge, they will be followed up on an outpatient basis by researchers, who will remotely supervise a physiotherapy program. Our hypothesis is that PES will positively influence the recovery of sensory function in patients undergoing neurorrhaphy of digital nerves of the hand.

**ReBEC registration:**  U1111-1259-1998 (12/18/2020)

## Introduction

### Peripheral nerve injury and regeneration

Damage to the peripheral nervous system (axonal damage) can occur due to a variety of reasons including trauma, ischemia, or inflammation (
Stoll & Müller, 1999). In response to peripheral nerve injury, morphological and functional changes can occur (
Knight, 2000;
Robbins, 1974), such as motor and sensory function impairment, hyperesthesia, and low-temperature intolerance (
Rosén & Lundborg, 2000). The process of extensive degeneration that occurs when the axon distal to the injury degenerates is known as Wallerian degeneration, however, the proximal stump, which remains attached to the cell body, can regenerate, and grow towards the target organ (
Stoll & Müller, 1999).

Neural regeneration following injury is influenced by a number of factors, such as age, level and extent of the injury, time elapsed from injury to repair, and presence of associated injuries (
Dunlop *et al.*, 2019;
Ruijs *et al.*, 2005). Axonal regeneration is influenced by chemotactic and electrical tracks (
Song *et al.*, 2004;
Stoll & Müller, 1999): if the tracks are not adequate (high or long), or the distance to be covered by the axonal sprouts is too large, the regenerated neurons will not be functional. This is the case of proximal injuries occurring close to the cell bodies, such as traumatic injury to the brachial plexus and injury of nerve roots in the conjugation foramen (
Gordon *et al.*, 2003). When the metabolism or nutrient supply is affected, such as in diabetes, functional regeneration is also impaired (
Kennedy & Zochodne, 2005). Therefore, promoting functional regeneration is key for the peripheral nervous system to resume normal functions.

Strategies to improve peripheral nerve regeneration include the use of neurotrophic factors, stem cells (
Lopes *et al.*, 2006;
Tohill & Terenghi, 2004), ultrasound (
Crisci & Ferreira, 2002), low-intensity LASER (
Bae *et al.*, 2004), physical exercise (
Molteni *et al.*, 2004;
Seo *et al.*, 2006), and electromagnetic fields. The latter is based on the fact that tissue injury results in an influx of calcium that causes endogenous electrical currents by increasing local electrical potentials (
McCaig *et al.*, 2002;
Watson, 1998). These currents are formed through electrical gradients between the affected area and the surrounding regions and remain active throughout the regenerative process (
Low & Reed, 2001). Exogenous electrical stimulation has been used to promote neural regeneration and early tissue recovery following injury.

### Electric fields and peripheral nerve regeneration

Electrical stimulation to improve the rate and speed of peripheral nerve regeneration involves the application of electrical fields of constant or varying frequency, as demonstrated in animal studies (
[name] *et al.*, 2007,
2008). Electrical currents are usually used, either flowing unidirectional (monophasic, constant or pulsed electrical currents) or bidirectional (alternate or biphasic electrical currents). The electrical currents may be administered through electrodes implanted in the nerve itself, intraoperatively, and using percutaneous or transcutaneous stimulation. Monophasic electrical currents have the advantage of unidirectionality; they can generate electrophoretic effects on membrane proteins and, thus, guide neurite growth towards the cathode (
McCaig *et al.*, 2002). However, if used at high intensity or for long periods, the monophasic electrical currents can cause harmful effects due to electrophoresis itself (
Low & Reed, 2001). Although biphasic currents do not offer the risk of harmful electrophoretic effects, they are less commonly used, as they do not have the power to guide the neurites towards the target organ.

There are different types of electrodes, with some predominating over others. In general, the closer the electrode is to the nerve, the smaller the current amplitude, as there is no need to overcome the impedance exerted by the surrounding tissues.

**
*Implanted electrodes.*
** Stimulation with implanted electrodes and different types of electrical currents have been the most used method since the 1980s in experimental models, generally for lesions in the soleus (
Nix & Hopf, 1983) and sciatic (
Beveridge & Politis, 1988;
Kerns *et al.*, 1991;
Mendonça *et al.*, 2003;
Politis *et al.*, 1988;
Pomeranz & Campbell, 1993) nerves. All of these studies showed positive results, with improvements in functional and/or morphological parameters.

Only two studies—one on lesions of the common fibular nerve (
McGinnis & Murphy, 1992) and the other on lesions of the sciatic nerve (
Hanson & McGinnis, 1994)—reported negative results, with fewer regenerating fibers, formation of neuromas, and a lower rate of myelination in the stimulated groups. However, in these studies, one of the electrodes was placed inside a small silicone tube that joined the two sectioned stumps, leading to the interaction of the single-phase electric current with the material of the tube. Deleterious effects arose due to the lack of alternating current and, consequently, destruction of part of the tube, with physical impediment to the passage of neurites.

To avoid tissue destruction, although the electrical currents used in all of the above-mentioned studies were monophasic, electrical current amplitudes were extremely low (below the sensitive threshold in the μA range). Stimulation was usually performed continuously for a few weeks prior to analysis.

**
*Percutaneous electrostimulation.*
** Percutaneous electrodes are usually acupuncture needles inserted into the skin and connected to an electric current generator. Electric currents through percutaneous electrodes have been used in experimental models and perhaps they are, of the methods studied so far, the simplest to apply in clinical practice. This type of stimulation has been used in models of sciatic nerve injury (
Chen *et al.*, 2001;
Inoue *et al.*, 2003;
McDevitt *et al.*, 1987;
Pomeranz *et al.*, 1984), with the best results achieved when the cathode was placed distal and the anode proximal to the lesion. Monophasic electrical currents were used, with amplitudes below the sensory threshold, yet reaching the intensity of 1 mA (much higher than that used in techniques with implanted electrodes).

**
*Intraoperative electrostimulation.*
** In intraoperative electrostimulation, the nerve is stimulated shortly following injury, for varying periods of time. Studies on intraoperative electrostimulation have mostly used the sciatic (
Scott, 1991) and femoral (
Al-Majed *et al.*, 2000a,
2000b,
2004;
Brushart *et al.*, 2002) nerves. The first studies used monophasic electrical currents; the most recent ones used alternating currents with pulse frequencies of 20 Hz (
Al-Majed *et al.*, 2000a,
2000b,
2004;
Brushart *et al.*, 2002). The latter allowed more precise and faster reinnervation; increased the expression of brain-derived neurotrophic factor (BDNF), tyrosine receptor kinase B (TrKB), Tα1-tubulin, and growth associated protein 43 (GAP-43), and other genes/proteins associated with regeneration; and reduced expression of neurofilaments (a phenomenon associated with regeneration). This model has been the only one to be translated to humans, so far.
Gordon *et al.* (2010) evaluated the same electrical stimulation protocol in patients with denervation of the muscles of the thenar region due to carpal tunnel syndrome. They observed that the treatment accelerated axonal regeneration without affecting function. Intraoperative electrostimulation differs from others, in addition to the form of stimulation, for the brief time it is used (approximately 1–2 hours of stimulation following injury).

**
*Thin-film wireless implantable nerve stimulators.*
** Using widely established technology, wireless devices dedicated to peripheral nerve stimulation have been used to improve functional recovery in a rodent model, without the additional time needed to provide direct stimulation during the surgical procedure (
Ray *et al.*, 2017). This strategy has not yet had practical application in humans.

**
*Surface electrodes.*
** The use of transcutaneous surface electrodes is a non-invasive option that can be used for a longer period, especially when associated with biphasic electrical currents. Its handling is practical and simple, avoiding the reactions provoked by implant surgery or percutaneous stimulation.

Previous studies have evaluated the influence of peripheral electrical stimulation (PES) through surface electrodes on the regeneration of tissues such as tendons (
Burssens *et al.*, 2003,
2005), skin (
Kaada & Emru, 1988;
Kjartansson *et al.*, 1988;
Khalil & Merhi, 2000;
Liebano *et al.*, 2003), and bone (
Kahn, 1982), with varying results. This modality is associated with effects such as increased blood flow (from
Sandberg *et al.*, 2007;
de Vries *et al.*, 2007) and collagen synthesis (
Burssens *et al.*, 2005). However, electrical currents with amplitudes above 1 mA are needed, which may be related to decreased concentrations of adenosine triphosphate (ATP) (
Cheng *et al.*, 1982) and, consequently, inhibition of peripheral nerve regeneration.

Electrical fields may influence blood circulation/perfusion, promoting an increase in axonal sprouting and nerve regeneration (
McCaig *et al.*, 2005). Low frequency electrical currents can selectively activate sensory C fibers and increase the expression of neuropeptides such as substance P, which generate vasodilation (
Burssens *et al.*, 2005;
Kashiba & Ueda, 1991;
Kjartansson *et al.*, 1988). Also, low-frequency PES (2–10 Hz) is usually associated with rhythmic muscle contraction, which can have circulatory effects (
Dobsák *et al.*, 2006). However, recent evidence has suggested that high-frequency PES, which is used without producing muscle contraction, also increases circulation.
de Vries *et al.* (2007) demonstrated an increase in coronary circulation as a result of high-frequency PES.

The most studied effects of PES are related to pain control. Analgesia caused by high-frequency PES activates δ-opioid receptors, while low-frequency PES activates μ-opioid receptors (
Kalra *et al.*, 2001;
Sluka & Walsh, 2003).
Sinatra & Ford (1979) demonstrated that the chronic use of morphine for 14 days leads to a delay in peripheral nerve regeneration, as reflected by a lower number of axonal profiles, decreased removal of myelin debris, and hypertrophy and proliferation of Schwann cells.
Zeng *et al.* (2007) also demonstrated that exposure to morphine, acting via μ-opioid receptors, increases the regeneration of unmyelinated fibers, while inhibiting the regeneration of myelinated fibers after ischiatic nerve crush injury.

The fundamental difference between the studies that showed stimulating or inhibitory effects on the regeneration of the peripheral nervous system via the activation of opioid receptors was the prolonged time of use, which may have led to the development of pharmacological tolerance.
Chandran & Sluka (2003) demonstrated that repeated high- and low-frequency PES for 20 minutes a day, led to opioid tolerance on day 4.
Mao *et al.* (2002) demonstrated that this effect is mediated by the
*N*-methyl-D-aspartate (NMDA)–caspase pathway, which leads to apoptosis of neuronal cells in the spinal cord. Therefore, the prolonged use of PES can lead to the development of opioid tolerance and neurotoxicity of the cells involved in regeneration. A brief use of PES, which does not lead to opioid tolerance, could however, be an important strategy to promote regeneration (
de Assis *et al.*, 2014), but this has not so far been investigated in humans.

### Objectives

Our overall aim is to study the influence of PES on peripheral nerve regeneration in humans. Specifically, we will study the influence of PES on recovery of sensory function, and on the social participation of patients undergoing neurorrhaphy of digital nerves of the hand.

### Protocol

This is a randomized, double-blinded, controlled clinical trial that will be carried out in a reference tertiary general hospital in Bahia, Brazil. This protocol has been registered at ReBEC (U1111-1259-1998 on 18
^th^ December 2020) and follows the Standard Protocol Items: Recommendations for Interventional Trials (SPIRIT) checklist (
[name] *et al.*, 2021d). Patients undergoing neurorrhaphy for injuries caused by transection of digital nerves in the hand will be involved in the study. Half the participants will have PES (Endophasys, KLD, Brazil) performed immediately after surgery and before hospital discharge and the other half will receive a SHAM treatment. The participants and outcome assessors will be blinded to patient allocation. The electrodes will be placed in the same position and for the same amount of time for the intervention group as the sham group. The outcome measures evaluators will not know which intervention was assigned to the participants.

### Participants

A convenience sample of adult patients (over 18 years old of both sexes) with acute traumatic non-segmental digital nerve injury referred from others health centers to the General Hospital of the State of Bahia to undergo surgical repair within a maximum of 2 weeks after the injury will be included. Patients with metal implants at the surgery site, who have a history of seizures, who have a cardiac pacemaker, or who have a local infection or skin lesion that prevents the application of surface electrodes will be excluded from the study.

### Materials

Basic material: Endophasys Electrostimulator – KLD, Brazil and silicone-carbon electrodes (used to perform electrostimulation in the patients).

All materials required for this study are available as extended data (
[name] *et al.*, 2021a).

### Setting

The Hand Surgery Service of the General Hospital of the State of Bahia is the foremost public tertiary trauma hospital and act mainly as referral center for other institutions in Bahia, Brazil. Outpatient Federal University of Bahia Physiotherapy Department will support the patients after surgery. The available facilities at these centers are listed in the extended data (
[name] *et al.*, 2021b).

### Intervention

Figure 1 shows a flow diagram of the participants’ journey through the study. Patients will be divided and allocated to two groups: group A (surgery + PES); or group B (surgery + sham). A simple randomization strategy will be performed to achieve balanced groups, using an online resource (
randomization.com). The hidden allocation and electrical stimulation will be performed by a professional not involved in other stages of the study. Opaque and sealed envelopes will be used to address participant allocation. Participants will only be randomized if they provide informed consent to participate in the trial.

**Figure 1. f1:**
[figure not shown]
Flow chart of the study based on CONSORT criteria.

Following surgery, both groups will additionally receive 1 hour of either electrical stimulation (group A) or sham (group B). In total, two silicone-carbon and gel electrodes (measuring 1 × 1 cm) will be used for all participants, with one placed exactly proximal and the other exactly distal to the surgical site. The two groups will receive the following therapeutic regimens:
•
*Group A: Surgery + PES.* The electrodes will produce a square-pulsed, biphasic, symmetrical current at a frequency of 20 Hz, pulse width of 0.4 ms, and amplitude at the motor threshold of the median nerve, for 1 hour directly after surgery (n = 16);•
*Group B: Surgery + sham PES.* The electrodes will produce a square-pulsed, biphasic, symmetric electric current at a frequency of 20 Hz, pulse width of 0.4 ms, and amplitude at the motor threshold of the median nerve, for 1 hour directly after surgery (the same as Group A) but the electrostimulator will be turned on only until the patient is aware of it, after which the amplitude will be set to zero (n = 16).

In the first post-operative review, the patient will be evaluated by the doctor at the outpatient clinic. A physiotherapist specialized in the area and blinded to the intervention will guide on the rehabilitation protocol that will be monitored remotely by electronic means available to the patient (WhatsApp, Skype, etc.). Patients will undergo a hand sensory re-education protocol based on the one proposed by
Dellon & Jabaley (1982) for a period of 3 months. This protocol involves exercises for discrimination of static and dynamic touch and objects of different shapes, sizes, and textures guided by the physiotherapist, and the patient is also stimulated to perform a home program exercises. This will involve a total of 20 remote monitored sessions lasting about 30 minutes each, carried out, on average, twice per week. No videos or photos of the patients will be acquired to guarantee the patient’s privacy and data confidentiality.

Patients will be evaluated in person after every 10 treatment sessions by the main author of the study, who is responsible for the surgical and postoperative follow-up of the study participants but blinded to group allocation.

Participants must complete a total of 4 face-to-face assessments to document the results:
‐1 pre-intervention/electrical stimulation‐1-week post-electrical stimulation‐1 after 10 rehabilitation sessions‐1 after all 20 rehabilitations sessions

The research will be completed within 1 year.

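### The fixed last visit supports a conclusion on early sensory recovery only, and the stated between-arm tests leave out repair-to-pulp distance

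*Protocol article*

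**What the plan says.** All references are to the protocol article.

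- **Aim.** The Objectives section says "we will study the influence of PES on recovery of sensory function". No time horizon is attached.
- **Visits.** The Intervention section says "Participants must complete a total of 4 face-to-face assessments to document the results". These fall before stimulation, one week after it, after 10 sessions and, last, "1 after all 20 rehabilitations sessions". No later sensory reading is listed.
- **Pace.** "This will involve a total of 20 remote monitored sessions lasting about 30 minutes each, carried out, on average, twice per week". The same section puts the re-education programme at "for a period of 3 months".
- **Start.** Rehabilitation guidance follows the first outpatient review: "In the first post-operative review, the patient will be evaluated by the doctor at the outpatient clinic". No week is given for that review.
- **Eligibility.** The Participants section admits adults "with acute traumatic non-segmental digital nerve injury", with no restriction on level or on distance to the fingertip.
- **Allocation.** Randomization is simple, 16 per arm (Intervention; Sample size and patient allocation).
- **Test site.** The Outcome measures section places the monofilament test on the pulp of the affected finger and describes it as reflecting reinnervation of the target. It gives no equally explicit site for 2PD.
- **Between-arm analysis.** The Statistical analysis section names one-way ANOVA or Kruskal–Wallis, chosen by normality or type of data.
- **Determinants.** The Introduction lists influences on regeneration "such as age, level and extent of the injury, time elapsed from injury to repair, and presence of associated injuries", and adds that too long a distance leaves regenerated neurons non-functional.

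**The concern.** A test at the pulp can register recovery only once axons have arrived there, and arrival depends partly on how far they had to grow. The last visit comes at the same point of rehabilitation for every patient, whatever that distance. Two patients with the same biological response can therefore score differently at the last visit because one repair was closer to the fingertip.

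Three things are at stake. Variation in distance enters the residual of an unadjusted comparison and widens it. In patients with long distances, an effect of stimulation may not yet be visible, which dilutes the arm difference. With 16 per arm and simple randomization, the arms can differ in average distance by chance, and the stated tests cannot correct for it. A null result might then be reported as no effect on sensory recovery, when the data speak only to the first months.

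**Working it through.** **1. Timing of the last visit, from the article's own figures.**
- By pace: 20 sessions ÷ 2 per week = 10 weeks.
- By programme length: 3 months ≈ 13 weeks.
- Both run from the start of rehabilitation, so time from repair is T = start + 10 to start + 13. A start at week 1 (assumption) gives weeks 11–14, and a start at week 4 (assumption) gives weeks 14–17.

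**2. Could distance matter by then?** The article gives no growth rate, lag or distances, so everything here is assumed: growth of 1–2 mm/day, a lag of 2–4 weeks before outgrowth, and repair-to-pulp distance spread evenly over 20–100 mm.

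Reach = (T − lag) × 7 × rate. Share reached = (reach − 20)/80, limited to 0–1.

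At 1 mm/day with a 3-week lag:

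| Rehabilitation starts | T (weeks) | Reach (mm) | Reached | Not reached |
|---|---|---|---|---|
| week 1 | 11 | 8 × 7 = 56 | 45% | 55% |
| week 1 or week 4 | 14 | 11 × 7 = 77 | 71% | 29% |
| week 4 | 17 | 14 × 7 = 98 | 97.5% | 2.5% |

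Slow end: 1 mm/day, 4-week lag, T = 11 gives 7 × 7 = 49 mm, so 36% are reached and 64% are not. Fast end: at 2 mm/day with a 4-week lag and T = 11, reach is 98 mm and 2.5% are not reached; with shorter lags or later visits none are left. The range is therefore 0% to about 64%.

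**3. Chance imbalance.** Under the same assumed spread, SD = 80/√12 ≈ 23 mm. The standard error of the arm difference in mean distance is 23 × √(2/16) ≈ 8 mm, or about 8 days of growth at 1 mm/day.

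**4. What dilution could cost.** The article's sample size reproduces. For the repeated-measures interaction with f = 0.26, 2 groups, 3 measures, correlation 0.5 and sphericity 1:
- λ = f² × N × 3/(1 − 0.5) = 0.0676 × 26 × 6 ≈ 10.5, with df 2 and 48. Power is 0.811, and 26 is the smallest even N above 0.80.
- 26 × 1.2 = 31.2, taken to 32, where power is 0.89.

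If a share p of patients can show no effect and f shrinks to 0.26 × (1 − p):

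| p | Power, N = 26 | Power, N = 32 |
|---|---|---|
| 0 | 0.81 | 0.89 |
| 10% | 0.72 | 0.82 |
| 20% | 0.61 | 0.71 |
| 30% | 0.49 | 0.59 |
| 50% | 0.27 | 0.33 |

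This is an illustration only. It assumes that the borrowed effect size contains no such dilution already, and that unreached patients contribute nothing.

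**5. Price of adjustment.** A two-arm comparison of 32 patients has 30 residual degrees of freedom, or 29 with one covariate. With 26 completers it goes from 24 to 23. In return, residual variance falls by a factor of about 1 − r², where r is the within-arm correlation of distance with the outcome. The article gives no value for r.

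**The case against.** A reader might infer that a visit at about three months leaves the trial unable to answer its question. The article does not support that. The assumed range above includes no loss at all. Distal repairs may well be reinnervated by then, and the Outcome measures section presents the monofilament test as a way to follow patients while regeneration is under way.

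A reader might also infer that unreached patients carry no information on stimulation. That applies one growth rate and one lag to both arms, whereas the trial asks whether stimulation changes regeneration. An early window suits a treatment that speeds arrival. In the same model at week 10 after repair and 1 mm/day, shortening the lag from 3 weeks to 2 raises the share reached from 36% to 45%. By week 26 both figures are 100% and the difference has gone.

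Two limits on the evidence also stand. The Introduction's example of too great a distance is injury near the cell bodies, such as the brachial plexus and nerve roots, not digital nerves. And an article may leave the recording of level to a fuller protocol, so silence does not prove that distance goes unmeasured.

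Chance imbalance is random error already allowed for by the test, not bias. Adjustment removes the part due to distance and improves precision.

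What remains is what the article does fix: a last visit not set by level, no limit on level in eligibility, simple randomization, and between-arm tests that cannot use distance even if it is recorded.

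**Conclusion.** The point holds as an inexpensive improvement, not as a defect that invalidates the trial. The design can estimate a difference in early recovery of sensory function. It does not address recovery beyond about three months of rehabilitation, and its stated between-arm tests ignore a factor that the article itself counts among the determinants of regeneration.

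The size cannot be fixed from the article. The range of 0% to about 64% unreached, the 8 mm standard error and the power table all rest on assumed growth, lag, distances and start of rehabilitation. No single figure within that range should be reported as the expected loss. The conclusion itself needs none of these values. It needs only that distance varies between patients and influences a reading at the pulp.

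**What to change.** 1. Have the surgeon record repair-to-pulp distance in millimetres at operation, before the allocation envelope is opened. Stimulation begins only after surgery, so this order is feasible and keeps the covariate a true baseline value.
2. Replace the unadjusted between-arm comparison of SWM and 2PD with one that includes this distance: ANCOVA or a mixed model across visits, or an ordinal or rank-based analogue where the scale or distribution calls for it.
3. Word the objective and conclusion as early sensory recovery at about 3 months, and state that a null result does not exclude a later difference.

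The cost is one extra measurement per patient, one degree of freedom and a narrower claim. No extra patients or visits are needed.

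A later blinded SWM and 2PD reading at routine follow-up could be added. It is a trade-off: within the one-year study limit, late recruits might not reach it. The recommendation does not depend on it.

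### Assessments 3 and 4 are triggered by rehabilitation sessions completed, not by time since nerve repair, so follow-up time varies with attendance and a patient who stops early has no stated trigger for the final visit

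*Protocol article*

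**What the plan says.** The Intervention section of the protocol article lists four face-to-face assessments. The first precedes stimulation. The second is at "1-week post-electrical stimulation", and because stimulation directly follows surgery, this visit is in effect fixed in time since repair. The third is "1 after 10 rehabilitation sessions" and the fourth comes "after all 20 rehabilitations sessions". The prose above the list gives the same rule: "Patients will be evaluated in person after every 10 treatment sessions by the main author of the study".

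Three statements in that section link sessions to time. The sensory re-education programme runs "for a period of 3 months". It comprises "a total of 20 remote monitored sessions lasting about 30 minutes each, carried out, on average, twice per week". Guidance on rehabilitation follows a first post-operative review, which has no date.

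Under Outcome measures, the primary outcome is the Semmes-Weinstein monofilament test and two-point discrimination, compared over all four assessments. Under Data management, the Cold Sensitivity Severity Scale and the Pain Disability Index are given at the last evaluation. The Intervention section requires each participant to complete the four assessments, but does not say when or how a patient who stops sessions is assessed.

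**The concern.** The trial asks whether stimulation improves sensory recovery after nerve repair, and the article presents regeneration as a process with a rate and a speed. A treatment effect of that kind is read most cleanly by measuring both arms at the same time since repair. Here, two of the three post-stimulation occasions are set by how quickly a patient works through the sessions. A slow attender has had longer to regenerate by the 20-session visit than a fast one, so slow attendance can pass for better recovery.

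Attendance also happens after randomization. If recovery, pain or disability influences it, both the timing of the outcome and its availability become linked to the outcome itself. The planned tests (repeated measures ANOVA or Friedman within groups, one-way ANOVA or Kruskal-Wallis between groups) take each visit as a common occasion and make no allowance for differing elapsed time.

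A patient who stops before session 20 meets no stated condition for the final visit. If that visit is missed, both questionnaires are missed with it.

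**Working it through.** **Inputs (Intervention section):** assessment 3 at 10 sessions; assessment 4 at 20 sessions; average rate 2 sessions a week; programme length 3 months, taken as about 13 weeks; start of rehabilitation undated.

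**Formula.** Weeks from the start of rehabilitation = sessions completed / sessions per week. Time since repair adds the undated interval from surgery to the first session, which can differ between patients.

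**1. The article's own figures**
- At 2 a week: assessment 3 at 10/2 = 5 weeks; assessment 4 at 20/2 = 10 weeks.
- With the 20 sessions spread over 3 months: 20/13 = 1.54 a week, so assessment 3 at 10/1.54 = 6.5 weeks and assessment 4 at 13 weeks.
- Two a week for the full 13 weeks would be 2 × 13 = 26 sessions, not 20.

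The stated figures thus put the third visit at about 5 to 6.5 weeks and the final visit at about 10 to 13 weeks. The final visit has a spread of about 3 weeks, and the two ranges do not overlap.

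**2. Other rates (assumptions, not in the article)**

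| Sessions per week | Assessment 3 (week) | Assessment 4 (week) |
|---|---|---|
| 1 | 10.0 | 20.0 |
| 1.5 | 6.7 | 13.3 |
| 2.5 | 4.0 | 8.0 |
| 3 | 3.3 | 6.7 |

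Only with rates like 1 a week does one patient's third visit (week 10) coincide with the fourth visit of a patient attending twice weekly.

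**3. Sample size and the loss allowance.** The Sample size section gives effect size f = 0.26, alpha 5%, power 80%, two groups, three measures, correlation 0.5 and non-sphericity correction 1. For the interaction in a repeated-measures ANOVA, the noncentrality is f² × N × measures / (1 − correlation). At N = 26 this is 0.0676 × 26 × 3 / 0.5 = 10.55, on (2 − 1)(3 − 1) = 2 and (26 − 2)(3 − 1) = 48 degrees of freedom. Power is 0.811. At N = 24 it is 0.775, so the stated 26 is reproduced. Then 26 × 1.2 = 31.2, which gives 32 at 16 per group, as stated.

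If patients without a final visit left a complete-case analysis, power on the same inputs would be:

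| Completers of 32 | Lost | Power |
|---|---|---|
| 32 | 0% | 0.892 |
| 26 | 18.8% | 0.811 |
| 24 | 25% | 0.775 |
| 20 | 37.5% | 0.685 |

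The loss rates and the complete-case handling are assumptions. The table shows only that losing 6 patients uses up the allowance. The visit rule does not alter the required sample size.

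**The case against.** **Silence is not exclusion.** A reader might infer that patients who stop sessions have no final outcome. The article does not say so. It requires four assessments of each participant and allows 20% for losses, and a condensed article may leave missed visits to the full protocol. This stands: the most that can be said is that no trigger is given for such patients. It does not excuse the session-count rule, which the article states twice and which is therefore a choice made, not a detail omitted.

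**The length statements may be compatible.** The 3 months may describe the whole programme, home exercises included, with about 10 weeks of monitored sessions inside it. Also, 1.54 a week rounds to 2. This largely stands: the mismatch is mild. It still leaves the nominal date of the final visit open by about 3 weeks.

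**Wide spreads and overlapping visits are not shown.** A reader might infer that one patient's third visit will coincide with another's fourth. That rests on attendance rates absent from the article, and 20 weeks lies well beyond its 3-month programme. This stands.

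**Bias between arms is conditional.** Stimulation is a single one-hour session, and participants, physiotherapist and outcome assessor are described as blinded. A reader might infer that the arms will be measured at different times, but nothing in the article shows this. The remark on rehabilitation difficulties in the section on economic and social impact attributes them to the lack of a service, which the trial itself supplies. What remains is that recovery can affect attendance even under blinding, and that variation equal in both arms still adds noise.

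**Equal exposure is a rationale.** Counting sessions measures each patient after the same amount of rehabilitation, and the planned tests accept ordered visits. This carries some weight, but rehabilitation is background care common to both arms. Stimulation is the randomized factor, and its effect unfolds with time since repair.

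**Conclusion.** The concern holds as a badly set rule on visit timing. Assessments 3 and 4, two of the three post-stimulation occasions in the primary comparison, are defined by sessions completed, so time since repair varies with attendance. The article gives no trigger for the final assessment, or for the two questionnaires tied to it, in a patient who stops early. On its own figures the spread is modest: about 10 to 13 weeks for the final visit and about 5 to 6.5 weeks for the third, counted from a start of rehabilitation that is itself undated. Anything wider is assumed.

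The likely consequence is added noise in a comparison of 16 against 16; its amount cannot be computed, because the article gives no recovery rate or variance. Bias is possible if recovery affects attendance, but is not shown, and blinding makes a difference between arms less likely. The sample-size calculation is not affected. The change is worth making because it is cheap, not because the present rule invalidates the trial.

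**What to change.** Define assessments 3 and 4 by time since surgery, at times the sponsor chooses, each with a stated window. Anchor them to surgery and not to the start of rehabilitation, which has no date. State that every randomized patient is assessed at those times, with the questionnaires at the last one, whatever the number of sessions done. Record sessions completed by each visit as an adherence variable. Reconcile the 3-month, 20-session and twice-weekly statements so that they describe one schedule.

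The cost is wording and appointment scheduling; the number of visits and the staff stay the same. The downside is that some patients will be assessed before finishing their sessions, so the last assessment will not be post-rehabilitation for everyone. The adherence record makes that visible.
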